### Inclusion and exclusion criteria

Inclusion criteria for participants are histopathologically confirmed metastatic adenocarcinoma of the prostate or high-risk M0 stage recurrent PCa for which androgen deprivation or antiandrogen therapy is initiated no longer than 3 months before recruitment, willingness to participate and signing of informed consent (figure 1).

Exclusion criteria for participants are regular statin use at the time of recruitment or within 6 months of it, previous adverse effects during statin therapy, familial hypercholesterolaemia or very high total cholesterol (9.3 mmol/L or above), clinically significant renal (serum creatinine above 170 µmol/L) or liver insufficiency (serum alanine aminotransferase more than two times above the upper limit of normal range), and use of drugs that may interact with statins (St John’s Wort, HIV protease inhibitors, ciclosporin, macrolide antibiotics, fucidic acid, phenytoin, carbamazepine, dronedarone or oral antifungal medication) (figure 1).

### Study endpoints

Primary endpoint is the time to disease progression after starting ADT/antiandrogen therapy. Secondary endpoints are (1) PCa-specific mortality and overall survival, (2) change in serum cholesterol during the intervention and its role in predicting time to disease recurrence in the placebo arm, (3) occurrence of adverse tumour traits predicting development of castration resistance in circulating cell free DNA, (4) changes in fasting blood glucose during ADT, (5) occurrence of cardiovascular events during ADT and (6) Quality of life (QoL) during ADT.

### Study flow

Study flow and schedule is presented in figure 1 and table 2. Patients are recruited at urology outpatient clinic at urologists’ visits. If the inclusion criteria are met and the exclusion criteria are not and the participant signs informed consent form, he is given a study number (ranging between E-001 to E-400) and he receives either 80 mg atorvastatin or placebo according to the study arm randomly allocated for the study number. No blocking or other restrictions will be implemented for randomisation. Only the national study coordinator in each country will be able to see which study arm the participant has been randomised to. The participant will then receive first dose of the respective study drug randomised to his study number. The drug boxes and capsules containing atorvastatin and placebo will be identical in appearance. All researchers, nurses and study participants will remain blinded to the allocation sequence until termination of the study and closure of the study data.

**Table 2 T2:** Study flow and timing of the laboratory and blood sample collection

	Enrolment	Allocation	Follow-up‡			
Timepoint		0	6 months	12 months	18 months	24 months
Enrolment:						
Eligibility screen	x					
Informed consent	x					
Allocation		x				
Interventions:*						
Atorvastatin			x	x	x	x
Placebo			x	x	x	x
Assesments:						
Serum PSA (ng/mL)	x		x	x	x	x
Alkaline phosphatase (U/L)	x		x	x	x	x
Creatinine (µmol/L)	x		x	x	x	x
Serum creatine kinase (U/L)	x		x	x	x	x
Alanine aminotranspherase (U/L)	x		x	x	x	x
Fasting blood glucose (mmol/L)	x		x	x	x	x
Lipid levels (total cholesterol, LDL, HDL and triglycerides) (mmol/L)	x		x	x	x	x
Cell free DNA (subgroup)†	x					
QoL	x			x		x

*Allocation 1:1 to have eighter 80 mg atorvastatin or placebo daily

†Cell free DNA is measured before allocation and after occurrence of castration resistance.

‡Follow-up until disease recurrance, death or max. 10 years

HDL, high-density lipoprotein; LDL, low-density lipoprotein; PSA, prostate-specific antigen; QoL, quality of life.

Control visits are scheduled at 6-month intervals to suit common clinical practice. Control visits are done by a clinician, complemented with measurements done by a research nurse. For each control visit the participant returns remaining capsules from the previously delivered ration and will receive a new one according to his study number. Number of the remaining capsules will be counted and saved in the REDCap, trial database, to monitor compliance. In every visit, serum PSA (ng/mL), lipid levels (total cholesterol, high-density lipoprotein (HDL), low-density lipoprotein (LDL) and triglycerides, mmol/L), alkaline phosphatase (U/L), creatinine (μmol/L), and fasting glucose (mmol/L) will be measured (table 2) and the participant is asked about symptoms that are suggestive of metastases and about possible adverse effects of the study drug. Serum creatine kinase (U/L) and alanine aminotransferase (U/L) is also measured at each visit.

Blood samples are taken and stored at 6-month intervals to monitor changes in tumour markers and occurrence of adverse tumour characteristics after initiation of ADT. QoL during the intervention will be charted once a year using validated WHOQOL-BREF QoL questionnaire.^33^

Follow-up is continued until development of castration resistance, drop out from the study, death or maximum of 10 years. Participants developing castration resistance are given an opportunity to carry on with their assigned treatment as statins have been linked to longer cancer-specific survival. Unblinding will be performed after recruitment target has been reached and all participants have been followed for minimum of 12 months.

PCa treatment apart from the study drug will be up to the discretion of the attending clinician. All laboratory results, symptoms and possible imaging results will be recorded in the REDCap database. All clinical decisions regarding early chemotherapy and imaging will be made on the discretion of the clinician and recorded in the REDCap database.

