Study type	Interventional, allocation: randomised, Intervention model: parallel assignment with 1:1 allocation ratio, Masking: double blind (subject, caregiver, investigator, outcomes assessor), Primary purpose: prevention, phase III
Date of first enrolment	July 2019
Target sample size	400
Recruitment status	Recruiting
Primary outcome(s)	Castration resistance
Key secondary outcomes	Lipid levels, Prostate cancer mortality and overall survival, Circulating cell free DNA, Fasting blood glucose, Occurrence of cardiovascular events during ADT, Quality of life

ADT, androgen deprivation therapy.

The study will be carried out in collaboration between urological departments of University Hospitals and central hospitals in Finland, the Herlev University Hospital in Denmark, the Tartu University Hospital in Estonia and Vestfold Hospital Trust in Norway (table 1).

Study data are collected and managed using REDCap electronic data capture tools hosted at Tampere University.^31 32^ Only the primary investigators, study nurses and registered study coinvestigator from each participating site will have access to the platform. All laboratory results, symptoms and results from imaging studies done at the discretion of the attending clinicians are recorded in the database. All clinical decisions besides the study drug, for example, use of early chemotherapy, abiraterone or other drugs in adjunct with ADT will be up to the discretion of the attending clinician and allowed but will also be recorded in the REDCap database.

Follow-up is continued until development of castration resistance, death or maximum of 10 years. Participants are given the opportunity to carry on with the intervention even after development of castration resistance to observe effects on survival. Unblinding will be performed after recruitment target has been reached and all participants have been followed for minimum of 12 months.

Castration resistance is defined as either PSA progression (three consecutive rises of PSA measured at least 1 week apart with two >50% increases over the nadir and PSA >2 ng/mL) or radiological progression (appearance of two or more lesions in bone scan or soft tissue enlargement as per RECIST criteria) while serum testosterone is at the castrate level (<50 ng/mL or 1.7 nmol/L).

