### Stored blood samples

Separate whole blood (for RNA and DNA isolation), plasma and serum samples are taken at each control visit at 6-month intervals and stored for mass-spectrometric and nuclear MR-based determination of serum lipidome. These samples will also be used for RNA and whole genome sequencing of mutations and genetic modifications predicting disease recurrence and metastasis, such as BRCA1/2, ERG, MYC, TP53, ATM, PTEN and AR splice variants.^34 35^ Also hypoxia markers will be measured.^36^

For participants with confirmed metastases in the bone or soft tissues, amount of cell free DNA from the plasma will be measured before ADT initiation and again at castration resistance development for sequencing and detection of genetic modifications predicting metastases.^34 35^ Selected patients are also imaged with positron emission tomography (PET) scan using 18F-2-nitroimidazolpentafluoropropylacetamide (EF5)^37^ to monitor hypoxia and fluorine-18-fluorodeoxyglucose positron emission tomography (FDG-PET) to evaluate immune responses^38^ in the primary tumour and the metastases during the atorvastatin intervention.

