Subgroup analyses will be performed stratified by type of ADT or antiandrogen therapy initially selected; GnRH agonists/antagonists, antiandrogen, orchiectomy or other. Men who start with antiandrogen therapy often change to GnRH agonists/antagonists or orchiectomy when PSA increases during ADT. This is allowed and PSA recurrence during antiandrogen therapy is not considered as disease progression as serum testosterone needs to be at castrate level as well for meeting the primary endpoint.

Another subgroup analysis will be stratified by whether or not the participants have received local therapy (radiation or surgery) for PCa in addition to ADT and by type of additional therapy participant has received; docetaxel, abiraterone, enzalutamide or apalutamide at hormone-sensitive stage in addition to ADT.

All analyses will include only participants with available data, imputations will not be used. Detailed statistical analysis plan is published before final data analysis. All analyses are performed using SPSS V.27, Stata V.17 and R V.4 statistical softwares.

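### Scheduled assessments alone cannot verify castration resistance: testosterone is on neither visit list, and six-monthly PSA cannot show three consecutive rises before month 18

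*Protocol article*

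**What the plan says.** All references are to the protocol article.

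- **Definition** (Study setting, text after Table 1). The PSA route is "three consecutive rises of PSA measured at least 1 week apart with two >50% increases over the nadir and PSA >2 ng/mL". The alternative route is "radiological progression (appearance of two or more lesions in bone scan or soft tissue enlargement as per RECIST criteria". A condition is attached to both: "while serum testosterone is at the castrate level (<50 ng/mL or 1.7 nmol/L".
- **Condition repeated** (Statistical methods). A PSA rise on antiandrogen therapy does not count by itself, because "serum testosterone needs to be at castrate level as well for meeting the primary endpoint".
- **Schedule** (Study flow). "Control visits are scheduled at 6-month intervals to suit common clinical practice". The tests named for every visit are PSA, lipids, alkaline phosphatase, creatinine and fasting glucose, followed by "Serum creatine kinase (U/L) and alanine aminotransferase (U/L) is also measured at each visit". Table 2 has rows for the same tests at enrolment and at 6, 12, 18 and 24 months. Neither place lists testosterone or imaging.
- **Stored material** (Stored blood samples). Whole blood, "plasma and serum samples are taken at each control visit at 6-month intervals and stored".
- **Unscheduled results** (Study setting and Study flow). Imaging and other cancer management are left to the treating clinician, and all laboratory and imaging results go into the trial database.
- **Assumed medians** (Sample size calculation). Time to progression is taken as 12–15 months in de novo metastatic men and 33 months in men with recurrence after primary therapy.

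**The concern.** A required component of the primary endpoint is on no schedule. A man can show clear PSA or imaging progression and still be unclassifiable if nobody measured his testosterone. This matters most for men who start on antiandrogens. The article expects PSA rises in them that must not count as events, and only a measured testosterone value separates those rises from true events.

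The PSA rule also fits the visit calendar poorly. Its minimum spacing is one week, but the scheduled spacing is six months. If early events cannot appear on scheduled values, their detection and dating depend on how often each clinician orders extra tests and scans. That may differ between clinicians, centres and countries.

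**Working it through.** The document gives no figure of its own for when an event can first be seen, so there is nothing to reproduce. The check has four steps.

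**1. Is every endpoint component scheduled?**

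| Component | Required for | Visit list (Study flow) | Table 2 |
|---|---|---|---|
| PSA | PSA route | yes | yes |
| Imaging | radiological route | no | no |
| Testosterone | both routes | no | no |

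The two lists agree with each other, and both omit testosterone.

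**2. Earliest third rise on scheduled PSA.** Three consecutive rises need one reference value and three later values. Visits are at 0, 6, 12, 18, 24, 30, … months after allocation.

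- Nadir at enrolment: rises at 6, 12, 18, so month **18**.
- Nadir at month 6: rises at 12, 18, 24, so month **24**.
- Nadir at month 12: rises at 18, 24, 30, so month **30**.

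The primary analysis counts time from the start of ADT, which may precede recruitment by up to 3 months. On that clock the ranges are 18–21, 24–27 and 30–33 months.

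**3. Share of men already progressed by month 18.** Assume exponential times (not stated in the document) with the stated medians: share = 1 − 0.5^(18/median).

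- Median 12: 1 − 0.5^1.5 = 64.6%
- Median 15: 1 − 0.5^1.2 = 56.5%
- Median 33: 1 − 0.5^0.545 = 31.5%

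So more than half of the de novo metastatic men, and about a third of the recurrent men, would progress before a scheduled third PSA rise could exist. The mix of the two groups is not given, so no overall share can be stated.

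**4. Minimum follow-up.** Unblinding requires at least 12 months of follow-up. A man with exactly 12 months has scheduled PSA values after baseline at months 6 and 12 only. Two values cannot give three rises, so he cannot meet the PSA route on schedule.

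**The case against.** The strongest reply is that the schedule is not the only source of data. There is a radiological route, unscheduled laboratory and imaging results are recorded, and the one-week spacing plainly allows PSA tests between visits. All of this stands. A reader might infer that the trial cannot establish its primary endpoint, or that the definition and the schedule contradict each other outright. The document does not support that. It supports only that scheduled assessments are insufficient alone and that the testing which fills the gap is not standardised.

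A second reply is that this is a condensed article, and that Table 2 is not exhaustive: it has no row for the stored blood samples. The full protocol may schedule testosterone. That is possible, but the article does not skip the subject. It prints two itemised laboratory lists that both omit a test its own definition requires. If the full protocol has the test, the correction is only to the text.

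Two further inferences are tempting and should not be drawn.

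- *That unverified men drop out of the analysis under the available-data rule.* That rule excludes imputation. A man without a confirmed event still contributes follow-up time.
- *That a six-month grid cannot resolve the 3-month difference called clinically significant.* The log-rank test compares whole curves, both blinded arms follow the same schedule, and the powered effect is a hazard ratio of 0.65. With exponential times that is 12/0.65 − 12 = 6.5 months, 15/0.65 − 15 = 8.1 months, or 33/0.65 − 33 = 17.8 months. Simulation with 200 men per arm and assumed uniform censoring between 12 and 72 months gave the following power (ranges over two runs):

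| Control median | Exact dates | Six-month grid | Every event waits for a scheduled third rise |
|---|---|---|---|
| 15 months | 0.94–0.96 | 0.93–0.95 | 0.87–0.89 |
| 33 months | 0.84–0.85 | 0.82–0.83 | 0.71 |

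Type I error stayed at about 0.05–0.06. The grid alone costs one or two percentage points of power. The last column is an extreme that the document does not imply, since interim tests and scans are allowed.

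**Conclusion.** The point holds in this form: scheduled assessments alone cannot verify the primary endpoint. The testosterone gap is the firmer part. It is an inconsistency within the article, needs no assumption, and affects both routes to the endpoint. The PSA timing is exact arithmetic: month 18 after allocation at the earliest, or month 24 if the nadir is at month 6. Its weight depends on the population. Month 18 is later than the assumed median in de novo metastatic men and earlier than that in recurrent men. The shares of 56.5–64.6% and 31.5% rest on exponential times.

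The likely harm is events that cannot be classified and event dates that depend on local testing habits. Bias between the arms is not shown: with blinding, testing intensity should be similar in both. The correction is worth making because it concerns the primary endpoint and is cheap.

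**What to change.** 1. Add serum testosterone to Table 2 and to the visit list in Study flow, assayed in blood already drawn at each visit. For men already enrolled, assay stored serum where volume and consent allow. The article earmarks that serum for other work, so neither can be taken for granted.
2. Require a recorded testosterone value with any off-schedule PSA or imaging result used to declare an event. Six-monthly serum would not cover those events.
3. Reconcile the definition in Study setting, Table 2, the Study flow list and the antiandrogen paragraph in Statistical methods, so that they say how the three-rise rule is met between six-monthly visits.
4. In the same edit, reconcile the two castrate thresholds printed in the definition. With a molar mass for testosterone of 288.42 g/mol (a constant not in the document), 50 ng/mL is 50 × 1000/288.42 ≈ 173 nmol/L, about 100 times the other printed figure.

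An interval-censored sensitivity analysis, using the last negative and first positive dates, is optional and can be left to the SAP.

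The cost is one inexpensive assay per sample and a few lines of text. The scheduled assays need no new visits.

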**Figure 2 F2:**
[figure not shown]
Sample size estimation with power 0.8 as a function of HR. Calculation was made based on study by Harshman *et al.*^23^

The median time to disease progression is assumed to be 12–15 months for patients with de novo metastatic disease and 33 months for patients recurring after primary therapy.^3–7^ Therefore, the intervention will continue until castration resistance, death, or for maximum of 10 years. Post hoc follow-up will continue after the intervention. A 3 months’ difference in time to castration resistance between the study arms will be considered clinically significant.

It has to be noted that the number of studies published on this topic is low and, in the absence of randomised evidence on this topic, the power calculation is based on results of epidemiological study prone to residual bias. Therefore, an interim analysis will be performed after the first 100 participants have met the primary endpoint, that is, progressed into castration resistance. Without lifting the blinding, the power calculations are repeated to verify whether the chosen sample size has adequate statistical power to detect statistically significant difference of the effect size observed between the randomisation groups at that time. If the calculations suggest that a larger sample size is needed for the trial, the study protocol will be amended with updated recruitment target.

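### Quality of life is first re-measured at month 12 while follow-up ends at castration resistance, so the available-data comparison partly depends on the primary outcome

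*Protocol article*

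**What the plan says.** Study endpoints lists "Quality of life (QoL) during ADT" as the sixth secondary endpoint. On timing, Study flow says "QoL during the intervention will be charted once a year using validated WHOQOL-BREF QoL questionnaire". Table 2 agrees: among its columns (enrolment, allocation, months 6, 12, 18 and 24) the form is marked at enrolment, month 12 and month 24 only. Visits at months 6 and 18 take place, but without the questionnaire.

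On the end of observation, Study flow says "Follow-up is continued until development of castration resistance, drop out from the study, death or maximum of 10 years", and the footnote to the follow-up columns of Table 2 says "Follow-up until disease recurrance, death or max. 10 years". Study setting gives the same end points. Both sections let men carry on with the assigned treatment after resistance, but neither gives a questionnaire schedule for that period.

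On the expected time to progression, Sample size calculation (below Figure 2) says "The median time to disease progression is assumed to be 12–15 months for patients with de novo metastatic disease and 33 months" for recurrence after primary therapy.

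On analysis, Statistical methods compares the arms item by item with a chi-square test and states "All analyses will include only participants with available data, imputations will not be used".

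**The concern.** In de novo metastatic men the first post-baseline questionnaire falls close to the assumed median time to the event that ends follow-up. A man who progresses earlier may contribute a baseline score and nothing else. Whether a man has a month 12 or month 24 score then depends on whether he has progressed, which is the outcome atorvastatin is meant to change.

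If the drug works, the arms keep different numbers of men, and possibly different kinds of men, in the quality-of-life data. Randomisation no longer protects that comparison. If the drug does not work, the scores still mainly describe slower progressors. The analysis plan cannot repair this later, because it cannot recover forms that were never collected.

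**Working it through.** The protocol states no expected questionnaire completeness, so there is no figure of its own to reproduce. The check asks how many men would still be progression-free at each possible questionnaire time.

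**Inputs.** Placebo medians of 12, 15 and 33 months and the 3-month clinically significant difference (Sample size calculation, below Figure 2); hazard ratio 0.65 (Sample size calculation); questionnaires at months 12 and 24 and visits every 6 months (Study flow, Table 2).

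**Assumptions.** Exponential times and proportional hazards; deaths without progression and other drop-out ignored. ADT may have been "initiated no longer than 3 months before recruitment". Under an exponential model this lag does not change the share progressing in the 12 months after entry among men who enter without resistance.

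**Formula.** Progression-free share at month t: placebo S(t) = 0.5^(t/median); atorvastatin S(t) = 0.5^(0.65·t/median). For example, at median 12 and t = 12: placebo 0.5^1 = 50.0%, atorvastatin 0.5^0.65 = 63.7%.

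Progression-free, placebo / atorvastatin (gap in points):

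| Placebo median | Month 6 | Month 12 | Month 24 |
|---|---|---|---|
| 12 (metastatic) | 70.7 / 79.8% (9.1) | 50.0 / 63.7% (13.7) | 25.0 / 40.6% (15.6) |
| 15 (metastatic) | 75.8 / 83.5% (7.7) | 57.4 / 69.7% (12.3) | 33.0 / 48.6% (15.6) |
| 33 (recurrent) | 88.2 / 92.1% (4.0) | 77.7 / 84.9% (7.2) | 60.4 / 72.1% (11.7) |

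**Progressed by month 12** (100% minus the share above). Metastatic: placebo 43–50%, atorvastatin 30–36%. Recurrent: 22% and 15%.

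**Allowing for detection at visits.** Suppose resistance is found only at the 6-monthly visits and a man whose resistance is found at month 12 still completes the form due that day. Then the men with no post-baseline score are those progressed by month 6. Metastatic: placebo 24–29%, atorvastatin 17–20%.

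**A smaller treatment effect.** Replace the hazard ratio by the protocol's 3-month difference in medians (12 to 15, 15 to 18, 33 to 36).
- Month 12: 57.4 − 50.0, 63.0 − 57.4 and 79.4 − 77.7, so gaps of about 7, 6 and 2 points.
- Month 24: 33.0 − 25.0, 39.7 − 33.0 and 63.0 − 60.4, so gaps of about 8, 7 and 3 points.

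**In numbers of men.** The mix of disease types is not stated. If half of each arm of 200 were metastatic (assumption), month 12 would leave 128–135 placebo and 149–155 atorvastatin men progression-free. For placebo at median 12: 100 × 0.500 + 100 × 0.777 = 128.

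**The case against.** The strongest reply is that the article does not say that progressed men give no scores. It charts quality of life during the intervention and lets men stay on the intervention after resistance, so those who continue may go on giving yearly forms. Men who discontinue or deviate may return to follow-up, and post hoc follow-up after the intervention is mentioned. This stands in part. A reader might infer that the comparison is confined to men who have not progressed, and the text does not go that far. But continuation is optional and self-selected, no post-resistance form is scheduled, and the offer to return concerns men who discontinue or deviate, not men who reach the planned end of follow-up.

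Second, progression is not the same as leaving. With 6-monthly visits some resistance will be found at month 12, where a form is due. PSA progression needs three consecutive rises, which scheduled PSA tests alone could not complete before month 18. This also has force. Against it, extra PSA tests and imaging at the clinician's discretion can show resistance sooner, and detection as late as month 18 would sit badly with the assumed 12–15 month median.

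Third, hazard ratio 0.65 comes from an observational cohort that the protocol itself calls prone to residual bias. At the 3-month difference the gaps are roughly half as large or less. That is correct, so both are shown.

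Fourth, the endpoint is the last of six secondary endpoints, the yearly schedule is consistent between text and table, and the primary analysis is untouched. All true. The model and main timepoint can be settled in the analysis plan; the collection schedule cannot be settled after the visits have passed.

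**Conclusion.** The point holds for a secondary endpoint, with moderate size. The schedule, the end of follow-up at resistance and the available-data rule together make the quality-of-life comparison partly conditional on the primary outcome.

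A reader might infer that about half of metastatic men leave before any post-baseline score. That is only the upper end: placebo men, the 12-month median, and every progression taken as departure before the form. Detection at 6-monthly visits brings the range down to 24–29% on placebo and 17–20% on atorvastatin, and later detection or optional continuation would lower it further.

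The difference in availability between arms at month 12 is 7–14 points if the hazard ratio is 0.65 and about 2–7 points at the 3-month difference. These figures rest on exponential times at the protocol's medians; additional therapy, which the protocol permits, could lengthen time to resistance and reduce them. The documents give no basis for saying which way scores would be biased, or by how much.

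**What to change.** Add WHOQOL-BREF to the month 6 and month 18 visits that Table 2 already schedules, and to the visit at which castration resistance is declared. The protocol already ties a cell-free DNA measurement to resistance, so collection triggered by that event is familiar to the sites. State whether men who continue the study drug after resistance go on completing the form.

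Compare the arms with a repeated-measures analysis adjusted for the baseline score that includes the resistance-visit score. A likelihood-based model of this kind uses the available scores and does not conflict with the no-imputation rule. The main timepoint can be left to the analysis plan. Month 6 is one candidate, but at hazard ratio 0.65 availability there would still differ by 4–9 points unless the resistance-visit score is used.

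The cost is an edit to Table 2 and one questionnaire at visits that mostly take place already, with slightly more burden for patients. Recruitment was open at publication, so men not yet at month 6 or at resistance could still benefit. The change reduces the selection; it does not remove it.
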